### Data collection, management, and statistical plan

#### Data collection

All RIs will be trained for trial electronic database use, injection technique, ROM, and grip measurements. For PRWE and Q-DASH questionnaires, forms on paper will be the primary data collection tools. When receiving the questionnaire forms, a trial nurse will make a visual check of the responses and queries for missing data when possible. Furthermore, the trial nurses will be educated on preparation of PRP, corticosteroid, and placebo. RIs will be blinded to group allocation and will store the forms in an electronic database by double data entry to minimize typing errors. Patient records will be reviewed when collecting missing data or interpreting inconsistent or implausible data.

#### Data management and monitoring

A database including patients’ identification information and consent forms will be generated. This database will also include the identification code given to each patient and the intervention. Questionnaire forms on paper are the primary data collection tools for the study. As the questionnaire forms are received, a study nurse will make an inspection of the responses and inquire missing data when possible. Research assistant, blinded to the group allocation, will store the forms into a password-protected electronic database on a hospital-provided server by double data entry to minimize typing errors.

No separate data monitoring committee will be established. As collected outcome data is de-identified regarding trial group, the RIs and biostatistician can control for safety of the interventions during the trial without compromising concealment. An interim analysis of the de-identified data will be run after 40% of the patients are enrolled and followed for 6 months. If any concerns arise regarding trial safety, the concealment will be unveiled, and the trial will be discontinued.

To ensure correct execution of the study, audits may be conducted if deemed necessary. However, routine audits are not planned.

#### Sample size

The primary outcome measure is PRWE, and the primary hypothesis of our trial is that single injection of PRP is non-inferior to single injection of corticosteroid in the treatment of TF measured with PRWE total score. The non-inferiority margin is set at 11.5 points using the PRWE minimally clinically important difference [32, 33]. To exclude the non-inferiority margin, the trial will require 32 patients in each group to observe MCID (non-inferiority margin 11.5, SD 14) in PRWE scores between the trial groups with a power of 90% and using a one-sided type I error rate of 2.5%. We will recruit 117 patients to account for 20% loss during follow-up.

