### Cross-over, loss to follow-up, and missing data

Participants enrolled will be allowed to call for unveiling the concealment at any point of the trial (preferably no sooner than 6 months post-randomization). However, to minimize this, the following will be addressed prior to trial enrolment to ensure that potential participants:

* Are willing to receive any of the interventions

* Understand that treatments might not provide benefit

* Are willing to remain with their allocation for 6 months

In case the allocation is unveiled, the patient will be offered either a corticosteroid injection (cross-over or second injection) or open surgery under local anesthesia based on the patients’ preference.

We will document the number and proportion of patients eligible for and compliant with each follow-up. If the number of patients withdrawing from any arm of the trial is greater than the anticipated 20% at 6 months, an analysis of the demographic and prognostic characteristics will be performed between the individuals who withdraw and those who remain in the trial. Moreover, data may not be available due to voluntary withdrawal of patients, lack of completion of individual data items, or general loss to follow-up. Where possible, the reasons for missing data will be ascertained and reported. If judged appropriate, missing data will be imputed using MICE [35] and in concordance to the respective manuals of the questionnaires used. However, the main analysis will be done using the available (not the imputed) data.

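### The target of 117 patients covers about 18% overall loss, not the stated 20%, because the allowance was added to the required number instead of divided out; power is barely affected

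*Protocol article*

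**What the plan says.** In the protocol article, the Sample size section names the comparison of PRP with corticosteroid on the PRWE total score as primary. It gives the inputs ("non-inferiority margin 11.5, SD 14", 90% power, one-sided type I error 2.5%) and concludes that "the trial will require 32 patients in each group to observe MCID". The next step is the allowance for losses: "We will recruit 117 patients to account for 20% loss during follow-up". Trial design sets three arms at 1:1:1, so 117 means 39 per arm, and the requirement before losses is 3 × 32 = 96.

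The section on cross-over, loss to follow-up and missing data uses the same percentage. If withdrawals from any arm are "greater than the anticipated 20% at 6 months", those who withdraw are to be compared with those who stay. That section also bases the main analysis on observed data, with imputation only as a possible addition.

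**The concern.** A loss allowance should leave the required number after the stated share of recruited patients has gone. Taking 20% off 117 leaves fewer than 96, so the requirement of 32 per group, the 20% loss and the target of 117 do not fit together.

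The 20% cannot easily be read as a share of the required number. The later section treats it as the share of an arm that withdraws by 6 months, which is the primary time point. Because the main analysis uses observed data only, each lost patient reduces the number analysed. What is at stake is whether the published allowance is one that the design has, and whether the primary comparison loses power as a result.

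**Working it through.** **Inputs** (protocol article): margin 11.5, SD 14, power 90%, one-sided alpha 2.5%, 32 per group, 20% loss and 117 recruited, all from Sample size; three arms at 1:1:1 from Trial design. The true difference between PRP and corticosteroid is not stated; it is taken as 0.

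**Step 1: reproduce the 32.**
- n per arm = 2 × (z₀.₉₇₅ + z₀.₉₀)² × SD² / margin²
- = 2 × (1.95996 + 1.28155)² × 14² / 11.5² = 31.14, rounded up to 32.

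This matches the plan.

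**Step 2: reproduce the 117.**
- 32 × 1.20 = 38.4, rounded up to 39; 39 × 3 = 117.

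This also matches exactly, so the likely route is multiplication by 1.20.

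**Step 3: the inflation that 20% loss requires.**
- 32 / (1 − 0.20) = 40 per arm; 40 × 3 = 120. Check: 40 × 0.80 = 32.

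**Step 4: what 117 delivers.**
- At 20% loss: 117 × 0.80 = 93.6 remain against 96, or 39 × 0.80 = 31.2 per arm on average.
- Largest loss that keeps 96: 1 − 96/117 = 17.9% (21 patients).

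**Step 5: whole patients.**
- All arms: 23 of 117 lost is 19.7% and leaves 94, so at least one arm is below 32.
- The two primary arms: 15 of 78 lost is 19.2% and leaves 63, against 64 required.
- A single arm of exactly 39: 7 lost is 17.9% and leaves 32; 8 lost is 20.5% and leaves 31.

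The shortfall within 20% therefore appears on average or when losses are pooled over arms. It does not appear in an arm of exactly 39 whose own loss stays at or below 20%.

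**Step 6: power against the margin.** The normal approximation is Φ(11.5 / (14 × √(2/n)) − 1.96). For n = 32 this is Φ(3.286 − 1.960) = 90.8%. The t-test figures use the noncentral t distribution with 2n − 2 degrees of freedom.

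| n per arm | Normal approximation | t test |
|---|---|---|
| 32 | 90.8% | 89.9% |
| 31.2 | 90.1% | 89.1% |
| 31 | 89.9% | 88.9% |

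By either method, going from 32 to 31 per arm costs about 1 percentage point.

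**The case against.** The strongest reply has three parts.

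1. *Per arm, 39 is enough.* The requirement is stated per group and the withdrawal check is applied per arm. An arm of 39 within 20% loss keeps 32, as Step 5 shows. This stands for an arm of exactly 39. It does not rescue the sentence on sample size, which sets the 20% against the total of 117; there, 23 losses already leave 94.

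2. *The stated power survives.* The unrounded requirement is 31.14 per arm, and 31.2 exceeds it. The normal approximation, which reproduces the plan's 32, still gives 90.1%. This also stands. The t-test figure of about 89% should not be presented as damage done by the allowance, because by that method even 32 per arm gives 89.9%.

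3. *An allowance was made.* It was, and it amounts to 117 − 96 = 21 patients. The gap to 120 is 3 patients (2.5%).

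A reader might also infer that the 20% trigger for the withdrawal analysis has to be lowered to 18%. The documents do not support this. In an arm of 39, a rule set at more than 18% and one set at more than 20% both first apply at the eighth withdrawal. The existing trigger thus already fires at the patient who takes the arm below 32. It also only starts a comparison of patient characteristics and has no part in the power calculation.

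**Conclusion.** The point holds as a minor arithmetic inconsistency. The 117 was most likely obtained by multiplying by 1.20 where dividing by 0.80 was needed, and it covers about 18% overall loss, not 20%. At 20% the expected shortfall is 96 − 93.6 = 2.4 patients over three arms, and the cost is under 1 percentage point of power (90.8% to 90.1% by the normal approximation, 89.9% to 89.1% by the t test).

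Two stronger readings are tempting. One is that the plan makes no provision for loss; it provides for 21 patients. The other is that the trial is underpowered; power stays at about 89–90% at the stated loss.

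The result assumes a true difference of 0, the stated SD of 14, and a target split of 39 per arm. The averages also assume losses spread evenly over the arms.

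**What to change.** Restate the closing sentence of Sample size along these lines: *117 patients (39 per arm) retain 32 per arm with up to about 18% loss; at 20% overall loss about 31 per arm remain, with power still about 89–90%.*

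This costs one sentence. Enrolment, design, analysis and the target of 117 in the registry table stay as they are, and the stated allowance becomes slightly less favourable. Leave the 20% trigger for the withdrawal analysis unchanged. A full 20% allowance would instead mean a target of 120, three more patients, but the small effect on power does not call for it.

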#### Statistical plan

Statistical analysis will be performed with an intention-to-treat method. A statistical software program will be used for analyzing entered data (IBM SPSS Statistics for Windows, Version 25.0. Armonk, NY: IBM Corp. 2017). Blinded data interpretation will be used to diminish interpretation bias; therefore, the biostatistician will be unaware of the group assignments when performing the analyses [34].

Descriptive statistics will be presented as mean (standard deviation) or median (interquartile range) for continuous variables and count (percent) for categorical variables. Levene’s test will be used to examine the homogeneity of variance between groups, and Welch’s or Student’s *t* test will be used to compare the point estimates for the means of the intervention groups. Ninety-five percent confidence intervals will be calculated for the mean difference. Chi-square test or Fisher’s exact test will be used to assess categorical data. Repeated measures will be analyzed using generalized linear mixed models.

The criterion for statistical significance will be set at *p* = 0.025 (one-sided) or *p* = 0.05 (two-sided). All *p* values will be reported to three decimal places with those less than 0.001 reported as *p* < 0.001.

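### Choosing between Student's and Welch's t test by a Levene pre-test lets the one-sided error drift slightly above 2.5% if the smaller arm has the larger spread; naming Welch in advance avoids this at almost no cost

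*Protocol article*

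**What the plan says.** The Statistical plan section of the protocol article states that Levene's "test will be used to examine the homogeneity of variance between groups". The same sentence continues that Welch's or Student's t "test will be used to compare the point estimates for the means of the intervention groups". No other basis for choosing between the two tests is given. The section adds: "Ninety-five percent confidence intervals will be calculated for the mean difference". On significance it says: "The criterion for statistical significance will be set at" p = 0.025 (one-sided) or p = 0.05 (two-sided).

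The Sample size section sizes the trial on PRWE non-inferiority of PRP to corticosteroid: "The non-inferiority margin is set at 11.5 points", a single SD of 14, "with a power of 90" per cent and "using a one-sided type I error rate of 2.5" per cent. It requires 32 per group and plans to recruit 117 to cover 20% loss. On missing data, the section on cross-over and loss to follow-up says that "the main analysis will be done using the available (not the imputed) data".

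Generalized linear mixed models are named for repeated measures, but the text does not make them the primary non-inferiority analysis.

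**The concern.** A variance pre-test turns the comparison of means into a mixture of two procedures, chosen from the same data. At about 31 to 39 patients per arm, Levene's test often misses a moderate difference in spread, so Student's pooled variance is kept when it is not appropriate.

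That does little harm if the arms are of equal size. If they are unequal, the pooled standard error is too small when the smaller arm is the more variable one, and too large when the larger arm is. Because the main analysis uses the available data, arms can finish at different sizes even though allocation is 1:1:1.

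What is at stake is whether the 95% interval for the PRWE difference, read against 11.5, carries the 2.5% one-sided error that the sample size is built on.

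**Working it through.** **Inputs from the protocol.** Margin 11.5, SD 14, power 90%, one-sided 2.5%, 32 per group, 117 recruited (39 per arm), 20% loss, 1:1:1 allocation.

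**Assumed, because the protocol does not give them.** Levene's test at 5%, centred on the mean; SD ratios of 1.2 to 2.0 between the arms; normal data except where stated.

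**Reproducing the planned size.** n = 2 × (1.960 + 1.282)² × 14² / 11.5² = 31.1, rounded up to 32 per group, as stated. Exact noncentral-t power at 32 per group is 0.899.

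**Why arm size matters.** Take 39 per arm with 20% loss in one arm only: 39 × 0.8 = 31.2, so 31 v 39. Let the smaller arm have SD 19.6 and the larger SD 14 (ratio 1.4).
- True SE of the difference: √(19.6²/31 + 14²/39) = √(12.39 + 5.03) = 4.17.
- Pooled variance: (30 × 19.6² + 38 × 14²)/68 = 279.0. Pooled SE: √(279.0 × (1/31 + 1/39)) = 4.02.
- Ratio 4.02/4.17 = 0.96, so Student's interval is about 4% too narrow.
- With the sizes reversed, the pooled SE is 4.18 against a true 4.02, so the interval is about 4% too wide. With equal sizes the two SEs coincide.

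**Error rate at the margin.** Simulation with the true difference set at 11.5, 400,000 runs per scenario (Monte Carlo SE about 0.025 percentage points), SDs 14 × ratio v 14. The more variable arm is listed first. Each range covers ratios 1.2 to 2.0.

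| Arm sizes | Student always | Welch always | Levene, then choose |
|---|---|---|---|
| 31 v 39 | 2.75–3.45% | 2.48–2.53% | 2.56–2.68% |
| 28 v 36 | 2.74–3.54% | 2.46–2.53% | 2.55–2.75% |
| 25 v 39 | 2.99–4.37% | 2.48–2.53% | 2.61–2.93% |
| 39 v 31 | 1.87–2.26% | 2.46–2.53% | 2.33–2.50% |

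With equal sizes (32 v 32, 39 v 39) or equal SDs, the two-stage rule stayed at about 2.5%. Running Levene over three arms changed little: the maximum was 2.72% at 31 v 39 and 2.95% at 25 v 39.

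A separate run with SDs 17 v 12 gave the same picture for the two-stage rule: 2.5% at 31 v 31, about 2.7% at 31 v 39, about 2.9% (3.0% with three-arm Levene) at 24 v 38, and 2.3% at 39 v 31.

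**Why the excess stays small.** At 31 v 39, Levene rejects in 29% of runs at ratio 1.3, 44% at 1.4 and 95% at 2.0. Student's test survives mainly where the SDs differ only moderately and its error is modest. At large ratios the rule has mostly switched to Welch.

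**Skewed scores.** With gamma data of shape 1.5, unequal SDs and unequal sizes, Welch ran at 2.7% to 4.4% and the two-stage rule at 2.9% to 4.5%. Neither was consistently better.

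**Power with equal SDs and true difference 0.** At 32 v 32: Welch 89.92%, Student 89.94%, two-stage 89.94%. At 24 v 38: Welch about 87%, roughly 0.3 points below Student.

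**The case against.** The strongest reply is that the effect is negligible under the plan's own assumptions. The protocol gives one SD, so any difference in spread is supplied from outside. The larger error rates also need extreme attrition: from 39 per arm, 24 v 38 means 15/39 = 38% loss against 1/39 = 3%. If both arms lost 20% at random, the SD of the difference in completers would be √(2 × 39 × 0.2 × 0.8) = 3.5, so a gap of 14 is about 4 SDs. Loss that lopsided would raise attrition bias as a bigger problem than half a point of alpha. All of this stands, and it sets the size of the point.

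It is also fair that the choice rule, Levene's level and the number of arms tested are not written out and may sit in an analysis plan not shown here. The point does not rest on that gap. It rests on a pre-test that the protocol does name.

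Three stronger readings are tempting but not supported:
- A reader might infer that any inequality of size and spread breaks the 2.5%. It does not: when the larger arm is the more variable, the rule errs on the safe side.
- A reader might expect a mix of resolved and unresolved patients in the PRP arm to make the case for Welch. Such scores would be skewed, and under strong skew Welch showed no clear gain.
- A reader might extend the false non-inferiority argument to Q-DASH, pain, grip strength and range of motion. No margin is set for these outcomes, so it does not apply.

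**Conclusion.** The point holds as a minor one. On its natural reading, the plan lets a weak pre-test choose the standard error for the primary PRWE comparison. That rule exceeds 2.5% one-sided only when the smaller arm has the larger spread. The excess is about 0.1 to 0.2 percentage points with the planned 20% loss falling wholly in one arm, and about 0.3 to 0.5 points under heavy imbalance.

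These sizes rest on near-normal data, Levene at 5%, unequal SDs that the protocol does not state, and the inference that Levene's result decides the test and the 95% interval decides non-inferiority. A reader might conclude that the trial's error rate is seriously compromised. The figures do not support that, and the choice of test is unlikely to alter the trial's conclusion.

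**What to change.** Delete the Levene step. State in advance that comparisons of means use Welch's t test and its 95% confidence interval, including the PRP-minus-corticosteroid PRWE difference at 6 months judged against 11.5.

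This changes one sentence. It costs at most about 0.3 points of power when the SDs are truly equal and the arms are very unequal, and practically nothing at 32 v 32. The required 32 per group does not change. The main gain is one pre-named interval for the primary comparison. It should not be presented as protection against strongly skewed scores.

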## Background

Trigger finger (stenosing tenosynovitis, TF) is a condition of the tendons of the hand that causes triggering, snapping, or locking on flexion of the involved finger. TF can limit the range of motion of the affected finger and is frequently accompanied by pain in the palm of the hand [1]. TF is often considered under the category of “repetitive strain injury” [2]. The snapping of the finger is caused by the imbalance of the tendon sheath and the flexor tendon, or more precisely, thickening of the first annular pulley, the tendon, or both. Although known as tenosynovitis, no inflammatory changes have been observed in histologic studies [3]. While the condition has been recognized since 1850, the exact etiology of the condition remains unknown [4].

TF is a very common hand disorder with an incidence of approximately 3% in the general population [4]. The incidence increases to 10% among patients with diabetes [5]. Besides diabetes, gout, carpal tunnel syndrome, DeQuervain’s and Dupyutren’s disease, amyloidosis, and mucopolysaccharidosis are thought to be associated with TF [4]. TF occurs in women six times more frequently than men and is most common during the middle fifth to sixth decades of life. The ring finger is the most commonly affected finger [6].

Conservative treatment of TF is mainly based on corticosteroid injections around the tendon sheath, where it is hypothesized to decrease the tendon-sheath disproportion [7]. Nonsteroidal anti-inflammatory agents, massage, heat, ice, splinting, exercises, and stretches might also be considered as a conservative approach to relieve symptoms [8]. The short-term effect of a single corticosteroid injection has been evaluated to set between 60 and 92% [1], whereas the incidence of spontaneous recovery has been estimated to be as high as 20–29% [3]. There are three previously published randomized controlled studies comparing corticosteroid and saline injections for primary TF [9–11], advocating the use of corticosteroid injection. The short-term symptom resolution of corticosteroid versus saline injection in these studies was 54–64% versus 15–27%, respectively. While short-term results support the use of corticosteroid injection in primary TF, the efficacy seems to decrease over time and the long-term evidence is insufficient [12, 13].

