#### Symptom resolution

Symptom resolution is a consensus between the patient and doctor on the perceived benefit of the treatment and is rated as follows: 0 = no response; 1 = partial response, but not satisfactory, warranting further treatment; 2 = partial response, satisfactory, not warranting further treatment; and 3 = complete resolution of symptoms and signs.

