#### Global improvement

Global improvement is a patient-centered standpoint of perceived benefit of the intervention. Global improvement is evaluated using five-step Likert scale from (− 2) “Much worse” to (+ 2) “Much better.”

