Date of first enrolment	April 9, 2020
Target sample size	117
Recruitment status	Recruiting
Primary outcome(s)	Symptom resolution (rate of success), Patient-Rated Wrist Evaluation
Key secondary outcomes	Quick-Disabilities of the Arm, Shoulder and Hand; pain (Visual Analogue Scale); global improvement; grip strength; finger range of motion (ROM); complications

*PRP* platelet-rich plasma

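### The only test named for categorical outcomes ignores order, although global improvement is an ordered five-step scale; an ordinal method should be named for it

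*Protocol article*

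**What the plan says.** The Statistical plan section of the protocol article sorts variables into continuous and categorical. Means are compared by Student's or Welch's t test. For the rest, chi-square or Fisher's "exact test will be used to assess categorical data". A separate sentence covers visits: "Repeated measures will be analyzed using generalized linear mixed models". It names neither the outcomes nor the link function. No rank test, trend test or proportional-odds model appears.

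Under Outcome measures, "Global improvement is evaluated using five-step Likert scale", running from −2 (much worse) to +2 (much better). It is listed as a secondary outcome.

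Symptom resolution is described as a grade from 0 to 3, but Table 2 lists the primary outcomes as "Symptom resolution (rate of success), Patient-Rated Wrist Evaluation". In that form symptom resolution is a proportion.

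**The concern.** On the plain reading, a five-step rating is categorical data and falls under the chi-square or Fisher rule. Such a test asks whether the two distributions differ in any way at all. It spreads its power over 4 degrees of freedom, has no direction, and gives no effect estimate. The confidence intervals promised in the section are for mean differences only. The question for global improvement is directional: do patients on one treatment rate themselves better than patients on another? A test that uses the order answers that question with one degree of freedom and the same patients.

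What is at stake is efficiency and interpretability on one secondary outcome. There is no risk of a false positive, because chi-square holds its type I error.

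**Working it through.** **1. Patients available.** The plan's own sample size comes first. Inputs from the Sample size section: margin 11.5, SD 14, one-sided 2.5%, power 90%.

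n per arm = 2 × SD² × (z₀.₉₇₅ + z₀.₉₀)² / margin² = 2 × 196 × (1.960 + 1.282)² / 132.25 = 392 × 10.51 / 132.25 ≈ 31.2, rounded up to 32.

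32 × 1.2 = 38.4, rounded up to 39 per arm, or 117 in total. Both stated figures reproduce. A comparison of two arms on global improvement would therefore have about 32 patients per arm, and 39 if nobody is lost.

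**2. Analytic check.** Suppose the whole treatment difference lies along the ordered direction. A 1-df trend test with 80% power at two-sided 0.05 has noncentrality (1.960 + 0.842)² = 7.85. Chi-square on five categories has 4 df and critical value 9.488. With the same noncentrality its power is 59.5%. Repeating this:

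| Power of 1-df trend test | Power of 4-df chi-square | Loss (points) |
|---|---|---|
| 50% | 30.8% | 19.2 |
| 60% | 38.9% | 21.1 |
| 70% | 48.2% | 21.8 |
| 80% | 59.5% | 20.5 |
| 90% | 74.0% | 16.0 |
| 95% | 83.7% | 11.3 |

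**3. Simulation.** The article states no distribution or effect for global improvement, so both are assumed. Reference distributions were symmetric, uniform, or skewed towards improvement. The other arm was obtained by multiplying every cumulative odds by one common odds ratio (OR). Example: 5/10/20/30/35% from worst to best has cumulative proportions 5, 15, 35 and 65%, with odds 0.053, 0.176, 0.538 and 1.857. Multiplied by 3, these give cumulative proportions 13.6, 34.6, 61.8 and 84.8%, so the worse arm is 13.6/21.0/27.2/23.0/15.2%. With 32 per arm, chi-square detects this difference in 43% of trials and Wilcoxon in 66%, a loss of 23 points. At OR 4 the figures are 65% and 85%, a loss of 20.

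Pearson chi-square against the tie-corrected Wilcoxon test, two-sided 0.05, five steps, two arms:

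| Assumed OR | Chi-square, 32 per arm | Wilcoxon, 32 per arm | Loss across distributions, 32 to 39 per arm |
|---|---|---|---|
| 2 | 18–19% | 33–34% | 14–17 points |
| 3 | 43–45% | 67–68% | 22–25 points |
| 4 | 66–68% | 86–87% | 16–24 points |
| 6 | – | – | 5–17 points |

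The loss column covers more distributions than the two power columns. At OR 1.5 the loss is 4 to 8 points, because neither test has much power there. Type I error was near 5% for both tests. The simulation and the analytic check agree.

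**The case against.** **The plan never assigns global improvement to chi-square.** It could go to the mixed models, which can be ordinal, or be treated as a score in a t test, or be settled in a full protocol or SAP that is not shown. This stands in part: the assignment is an inference. But the article fixes a rule for categorical data and offers no ordinal alternative, while the mixed-model sentence names no outcome and no link. The point concerns a stated rule that fits this scale poorly, not detail the article left out.

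**Symptom resolution.** A reader might infer that the 0–3 grade is mis-tested too. The documents do not support that. Table 2 gives a rate of success, and the Background section reports earlier trials the same way: resolution with corticosteroid against saline "was 54–64% versus 15–27%, respectively". For two proportions, chi-square or Fisher is a proper test. Even if the four grades were tested, the simulated loss was 10–19 points at OR 2 to 4. If the Background rates are taken as the top grade, the loss is 0 to 17 points under proportional odds, and −1 to 7 if the lower grades keep their relative shares. This objection stands in full.

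**The size of the loss.** A reader might take 15 to 25 points as a general property of the plan. It is not. It fits a five-step scale at moderate effects, and proportional odds is a setting that favours the rank test.

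**Consequence.** A reader might also infer that the test of PRP against saline is compromised. The Trial hypothesis section does not tie that hypothesis to global improvement. The scale is one of several secondary outcomes and was not powered. Reported counts and percentages would still show the direction. All of this stands and limits the weight of the point.

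**Conclusion.** The point holds for global improvement only. The single rule given for categorical data ignores order, and this outcome is ordered. If the rule is applied at about 32 per arm, the loss against an order-using test is about 14 to 25 points for odds ratios of 2 to 4, and it narrows outside that range. The figure depends on assumed distributions and on proportional odds; the article supplies neither. Sample size and power for PRWE reproduce and are untouched, and type I error is not at risk. This is a cheap gain on a secondary outcome, not a flaw in the main analysis.

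**What to change.** Add one sentence to the Statistical plan section: global improvement is compared between arms by the Wilcoxon-Mann-Whitney test or a proportional-odds model, with a common odds ratio and its 95% confidence interval; if visits are analysed together, the mixed model for this outcome uses an ordinal (cumulative) link. State that chi-square or Fisher's exact test is kept for unordered and two-category outcomes, including the symptom-resolution success rate and adverse events. An ordinal analysis of the 0–3 symptom-resolution grades may be added as support, but is optional.

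The change needs no extra patients or data, and the methods are available in the software the plan names. It should be dated before the group codes are broken for the six-month analysis, so that the method is not chosen with results in view.
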